## Abstract

**Background:**

Age-related muscle wasting has been strongly implicated with falls and fractures in the elderly, but it has also been associated with cognitive decline and dementia. Progressive resistance training (PRT) and adequate dietary protein are recognised as important contributors to the maintenance of muscle health and function in older adults. However, both factors also have the potential to improve brain function and prevent cognitive decline via several pathways, including the regulation of various growth and neurotrophic factors [insulin-like growth factor-1 (IGF-1)]; brain-derived growth factor (BDNF)] and/or the modulation of systemic inflammation. The primary aim of this study is to investigate whether a modest increase in dietary protein achieved through the consumption of lean red meat three days per week, when combined with PRT, can enhance muscle mass, size and strength and cognitive function in community-dwelling older people.

**Methods/Design:**

The study design is a 48-week randomised controlled trial consisting of a 24-week intervention with a 24-week follow-up. Men and women (*n*=152) aged 65 years and over residing in the community will be randomly allocated to: 1) PRT and provided with 220 g (raw weight) of lean red meat to be cooked and divided into two 80 g servings on each of the three days that they complete their exercise session, or 2) control PRT in which participants will be provided with and advised to consume ≥1 serving (~1/2 cup) of rice and/or pasta or 1 medium potato on each of the three training days. The primary outcome measures will be muscle mass, size and strength and cognitive function. Secondary outcomes will include changes in: muscle function, neural health (corticospinal excitability and inhibition and voluntary activation), serum IGF-1 and BDNF, adipokines and inflammatory markers, fat mass and inter-/intra-muscular fat, blood pressure, lipids and health-related quality of life. All outcome measures will be assessed at baseline and 24 weeks, with the exception of cognitive function and the various neurobiological and inflammatory markers which will also be assessed at week 12.

**Discussion:**

The findings from this study will provide important new information on whether a modest increase in dietary protein achieved through the ingestion of lean red meat can enhance the effects of PRT on muscle mass, size and strength as well as cognitive function in community-dwelling older adults. If successful, the findings will form the basis for more precise exercise and nutrition guidelines for the management and prevention of age-related changes in muscle and neural health and cognitive function in the elderly.

**Trial registration:**

Australian New Zealand Clinical Trials Registry: ACTRN12613001153707. Date registered 16^th^ October, 2013.

## Background

Age-related loss in muscle mass, strength and function, which has been termed sarcopenia, has been linked to a range of common chronic diseases, including an increased risk for falls and fractures [1–3]. Although there is no single cause of sarcopenia, physical inactivity, inadequate nutrition and age-related reductions in circulating sex steroids, growth factors and vitamin D, and concomitant increases in pro-inflammatory cytokines such as interleukin-6 (IL-6), C-reactive protein (CRP) and tumor necrosis factor-alpha (TNF-α), have all been implicated [2, 4]. There is also strong evidence that dementia and related cognitive deficits in older people, particularly deficits in executive function such as the ability to concentrate, to attend selectively, multi-task and to plan and strategize, are associated with both risk factors for falls [e.g., postural instability, impaired gait, reduced ability to perform activities of daily living (ADL)] as well as future falls [5]. Other studies have also reported that low muscle mass and strength and muscle loss are associated with cognitive impairment [6–8] and brain atrophy [9]. Thus, identifying interventions that can optimize muscle mass, strength and function, and improve cognitive function are likely to provide the greatest benefits in terms of ensuring that older adults can live independently and relatively disease and disability free into old age.

Progressive resistance training (PRT) is promoted as one of the few lifestyle approaches that can significantly increase muscle strength, mass and size, but there remains considerable heterogeneity in the skeletal muscle responses to PRT in older adults [10, 11]. For muscle hypertrophy to occur there must be a net increase in muscle protein balance, that is, muscle protein synthesis (MPS) must exceed muscle protein breakdown (MPB). PRT can stimulate MPS above resting levels, but MPB also rises such that net protein balance remains negative in the fasted state [12]. While the provision of protein (amino acids) post-exercise can overcome this imbalance and result in a net positive protein balance, the anabolic sensitivity of skeletal muscle to protein appears to be blunted with ageing [12]. As a result, it has been suggested that older adults require a higher dose of protein to maximise MPS and promote muscle hypertrophy in response to PRT [12, 13]. Although the optimal dose of protein needed to enhance the anabolic response to PRT in older adults is not known, there is some evidence that a daily protein intake >1.2 to 1.5 g/kg body weight or 20–40 g of high quality protein ingested following PRT can promote MPS and muscle hypertrophy [13–16]. While most previous studies have focused on the effects of milk (whey and casein) and soy protein, red meat is another rich source of protein that contains complete and balanced proportions of all eight essential amino acids, and has been shown to promote MPS at rest and following PRT in older adults and the elderly [17–20]. For instance, it has been shown that ingestion of a 113 g (moderate) serving of beef (30 g protein) produced a 50 % increase in MPS [18], with no further gains following the ingestion of a larger 340 g serving (90 g protein) [20]. In a recent 4-month randomised controlled trial (RCT) in women aged 60 years and over, we found that ingestion of two ~80 g servings of cooked lean red meat on most days of the week enhanced the effects of PRT on muscle mass, strength and serum insulin-like growth factor-1 (IGF-1) and reduced inflammation [serum IL-6]; there were no adverse effects on blood pressure, lipids or kidney function [15]. Despite these positive findings, promoting daily consumption of red meat is not consistent with the current Australian Dietary Guidelines [21]. Thus further research is needed to determine whether less frequent consumption (e.g., an intake consistent with current dietary guidelines of no more than 455 g per week of cooked lean red meat) is equally effective when consumed in combination with exercise.

In addition to preserving muscle health in older people, recent attention has focused on identifying strategies to attenuate age-related cognitive declines as this has been identified as a key risk factor associated with falls and disability in the elderly [22], and precedes the development of dementia and Alzheimer’s disease [23]. Globally the prevalence of dementia is estimated to increase from around 35 million people in 2010 to around 115 million people by 2050, with many more people having some degree of cognitive impairment [24]. Currently there are no disease modifying pharmacological treatments to cure or delay the progression to dementia. However, regular exercise, including aerobic training, PRT or the combination, has been recognised as promising strategies that can induce a cascade of molecular and cellular processes which may improve brain function, structure and/or neural connectivity via several pathways, including the release of various growth and neurotrophic factors, and cognitive function, particularly measures of executive functioning and processing speed [25–29]. However, not all studies have reported beneficial effects of exercise on measures of cognition, which may relate to differences in the study populations, study duration, training dose (duration, intensity and/or frequency) and/or the dietary habits of individuals.

Previous research has shown that certain dietary patterns or nutrients can have a positive effect on neuronal plasticity and cognitive function among older adults [30–33]. Although the data from randomised controlled trials is limited, a number of reviews have highlighted that the findings from epidemiologic studies tend to support a protective role of omega-3 fatty acids, B-vitamins or antioxidants and the Mediterranean diet [30, 32, 33]. There is also emerging evidence that dietary protein and its constituent amino acids are associated with cognitive function in older adults [34–36]. In a population-based, prospective study (median follow-up 3.7 years) in 937 elderly aged 70–89 years who were cognitively normal at baseline, a higher dietary protein intake was associated with a 21 % reduced risk of mild cognitive impairment or dementia, independent of potential confounders [37]. While there are few intervention trials which have examined the effects of dietary protein or protein supplementation on cognition, a study in healthy young men demonstrated that a high-protein meat diet for 3 weeks improved cognitive function (reaction time for demanding tasks) [38]. Moreover, an Australian study reported that women habitually consuming less than the recommended intake of red meat were twofold more likely to experience depressive or anxiety disorders than those consuming the recommended amount [39]. Given that red meat contains other nutrients in addition to protein such as iron, zinc, several B vitamins, omega-3 fatty acids and possibly vitamin D which have all been linked to cognitive function, we hypothesise that combining a diet rich in red meat with PRT will be more effective for enhancing cognitive function and neural plasticity in older adults than PRT alone.

There are several lines of evidence to support our hypothesis. One of the proposed mechanisms by which exercise may improve cognition and neural plasticity as well as muscle health is via an increase in circulating IGF-1 and serum brain-derived neurotrophic factor (BDNF) and/or a reduction in systemic inflammation [40, 41]. It is well known that IGF-1 is central to muscle growth, but it has also been shown to have neuroprotective actions by promoting neuronal growth, survival and differentiation [40, 42]. IGF-1 has also been shown to augment BDNF concentrations, which is a neurotrophin that functions to support the growth and maintenance of neuronal circuits as we age [40]. Indeed, a number of human studies have reported a link between circulating BDNF concentrations and cognition [43, 44], and there is evidence that BDNF stimulates neurons to survive longer and branch and connect in new ways (synaptic plasticity) to promote memory and learning [40, 45] as well as executive function and processing speed [44, 46]. Finally, increased inflammation has also been linked to muscle loss and cognitive impairment, and associated with an increased risk of dementia [47, 48]. Building upon our previous 4-month randomised controlled trial in elderly women which showed that PRT combined with increased consumption of lean red meat on most days of the week resulted in a greater increase in serum IGF-1 and a reduction in circulating IL-6 levels compared to PRT alone, together with existing research which has shown that dietary protein and exercise can stimulate an increase in serum BDNF, we hypothesise that combining these approaches will be more effective at improving cognitive performance in older adults than exercise alone. In addition, by measuring changes in cortical plasticity using Transcranial Magnetic Stimulation (TMS), a painless and non-invasive technique that allows an assessment of neuroplasticity through cortical excitability and inhibition (eg. responsiveness of the entire neural pathway from the motor cortex to the muscle), this study will provide new data on the role of PRT combined with increased dietary protein on neural plasticity in the elderly.

The primary aim of this 24-week randomised controlled trial with a 24-week follow-up in community-dwelling older adults is to examine the effects of a multi-modal exercise program involving PRT combined with a protein-enriched diet achieved through lean red meat consumed three days per week (on training days) on skeletal muscle mass, size and strength, and cognitive function. The secondary aims of the study are to:Evaluate the effects of the intervention on physical functioning, neural plasticity (corticospinal excitability and inhibition and voluntary activation), various growth and neurotrophic factors and systemic inflammatory markers associated with muscle and cognitive health, and health-related quality of life;Explore whether any intervention related changes in cognitive function are modulated by body composition, neurotrophic markers, inflammatory cytokines, circulating growth factors, bioavailable zinc and cardiovascular risk factors;Determine if the 24-week supervised and structured exercise and protein intervention can lead to long-term behavioural changes with regard to maintaining participation in exercise and/or consuming a diet rich in red meat in older adults.

## Methods

### Study design

This is a 48-week randomised controlled trial consisting of a 24-week intervention with a 24-week follow-up. Men and women aged 65 years and over will be randomly allocated to one of two groups: 1) PRT with two 80g servings of cooked lean red meat on each of the three days that they complete their exercise session (RT+Meat group), or 2) control PRT in which participants will be provided with and advised to consume ≥1 serving (~1/2 cup) of rice and/or pasta or 1 medium potato on each of the three training days [control resistance training (CRT)]. On the non-training days, the red meat group will be instructed to maintain their usual diet whilst those in the CRT group will be asked to continue to incorporate larger servings of breads, cereals, rice, pasta and vegetables (carbohydrates) and smaller amounts of protein foods (e.g. meat, fish and chicken). All participants will be asked to take a daily vitamin D supplement (1000 IU) and encouraged to maintain a healthy diet that includes the recommended amounts of fruits and vegetables and dietary calcium throughout the entire study. At the completion of the 24-week intervention, all participants will be encouraged to continue to undertake the exercise program (at their own expense) and those in the red meat group were provided with dietary advice to maintain a protein rich diet (at least 1.2 g/kg/day) including red meat which will be monitored at weeks 36 and 48. The trial is managed by the Centre for Physical Activity and Nutrition Research at Deakin University, Burwood, Melbourne, Australia and is funded by a nationally competitive grant from Meat and Livestock Australia. The study has been approved by the Deakin University Human Research Ethics Committee (HREC 2013–166), and is registered with the Australian and New Zealand Clinical Trials Registry (ACTRN12613001153707).

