#### Lean red meat

Participants allocated to the red meat group will be supplied with ~220 g (raw weight) of lean red meat to be consumed on each of the three training days per week for 24 weeks to achieve a modest increase in mean dietary protein intake in mean dietary protein intake to a level of at least 1.3 g/kg/day. This equates to ~160 g of cooked meat per day (~45 g of protein). All participants will be asked to prepare the meals themselves and consume the meat at lunch and dinner (~80 g cooked serving per meal) as there is emerging evidence that a divided dose of protein spread throughout the day may be more effective for enhancing muscle protein synthesis than a single large dose in the evening [49]. The meat will be supplied in labelled 110 g portion packs trimmed of visible fat, and participants will select from a variety of veal, lamb or beef cuts, delivered frozen every 4 weeks by a local butcher. Participants living with a partner will also receive sufficient food supplies for their partner. For the other non-training days, participants will be advised to maintain their usual diet. All participants will be provided with instructions of how to maintain a daily protein rich diet (e.g. foods and recipes rich in protein) and will receive recipes and written dietary instructions for consuming the red meat. We have found that this dietary intervention in older women results in a modest average increase in dietary protein from 1.1 to 1.3 g/kg/day [15]. We therefore expect that participants will achieve an intake of approximately 1.3 g/kg/day for 3 days/week when exercising and around 1.1 g/kg/day for the remaining 4 days.

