### Sample size calculations

The number of participants required for this study is based on power calculations for the expected changes in total body lean mass, lower limb muscle strength and cognitive function, particularly executive function. Based on our previous study in elderly women [15], we estimate that 152 older adults in each group will provide >80 % power (P<0.05, two tailed) to detect a 0.5 kg and 18 % differences for the change in total body lean mass and leg muscle strength between the red meat and control group, assuming a standard deviation of 0.9 kg and 30 %, respectively. This calculation allows for a possible 20 % drop-out or loss to follow-up. For measures of cognitive function, it was difficult to provide an accurate estimate of the magnitude of any intervention effect (effect size) because this study is the first to examine the effects of exercise combined with increased dietary protein compared to exercise alone in older adults. Previous research examining the effects of exercise on measures of cognitive function report moderate effect sizes (*d* = 0.41 to 0.59) following PRT or aerobic training alone or in combination [25, 26, 73], particularly on measures of executive function and processing speed. Whether increased dietary protein can improve cognitive function in older adults remains uncertain, but we hypothesize that exercise combined with a modest increase in dietary protein (1.3 g/kg/day) will lead to a medium effect. Using data from a pilot study in 72 healthy older adults aged 65 years and over in which the mean (standard deviation, SD) scores on the CogState Groton Maze Learning Task (a measure of executive function) and the Detection Task (a measure of reaction time and processing speed) were 64 (18) and 2.56 (0.07) respectively, we anticipate that a sample size of at least 140 will provide approximately 80 % power (P<0.05, two-tailed) to determine a medium effect size (*f* = 0.20) assuming a 0.6 correlation among repeated measures.

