## Discussion

This community-based RCT will be the first to evaluate whether a multi-modal exercise program incorporating PRT in combination with increased dietary protein achieved through the consumption of two ~80 g servings of cooked lean red meat on each of the three training days is a safe and effective strategy to enhance muscle mass, size and strength and cognitive function in community-dwelling older adults. In addition, this study will determine whether such an intervention translates into long-term behavioural changes with regard to adopting a healthier lifestyle that incorporates regular participation in PRT and consumption of a diet high in protein (red meat). This is important because age-related muscle wasting and a decline in cognitive function have both been implicated in the development and progression of many chronic diseases, including falls and dementia. From a public health perspective, if the intervention proves to be effective, the pragmatic nature of the intervention, with the exercise conducted within local community-based health and fitness centres and dietary protein increased through the use of lean red meat at an intake equivalent to the current Australian dietary guidelines of 3–4 serves per week, should ensure that the program can be easily implemented and adopted and is applicable in real life.

Another strength of the study is that our secondary outcomes will provide a unique opportunity to: 1) evaluate the effects of the intervention on neural plasticity, and 2) identify potential biological determinants of exercise and protein-induced changes in cognitive function (and skeletal muscle health) in older adults. Specifically, this study will be one of the first to determine whether combining exercise with increased dietary protein (lean red meat) can have a positive effect on a range of neurobiological markers, including various circulating growth and neurotrophic factors (e.g., IGF-1, BDNF, VEGF) and systemic inflammatory cytokines in older adults, and whether any changes in these biological determinants in response to the intervention are associated with any changes in cognitive function and neural plasticity.

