In summary, we believe that the findings from this study will form the basis for more targeted nutrition and exercise guidelines for the management and prevention of age-related changes in muscle and neural health as well as cognitive function in older people. We anticipate that the findings from this study will provide direct evidence that the current guidelines to consume no more than 455 g of lean red meat is a safe, acceptable and effective dose and source of protein that can have beneficial effects on improving multiple health outcomes when combined with regular exercise. In addition, we expect that the results will also show that there are no adverse effect of this approach on cardiovascular-related health outcomes or kidney function. This is important because there are some concerns that a high red meat diet is associated with a number of adverse health outcomes, including an increased risk of heart disease, type 2 diabetes and certain cancers.

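### The protocol's weekly red meat and protein figures do not agree with each other, and the power statement assumes that less frequent meat works as well as the earlier, more frequent regimen

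*Protocol article*

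**What the plan says.** **Red meat.** Study design assigns "PRT with two 80g servings of cooked lean red meat on each of the three days" of training. The Lean red meat section describes the supply as about "220 g (raw weight) of lean red meat to be consumed on each of the three training days per week for 24 weeks" and adds "This equates to ~160 g of cooked meat per day (~45 g of protein"). On the other four days the meat group keeps its usual diet, and no limit on red meat is stated for those days. The Background motivates the trial by an intake of "no more than 455 g per week of cooked lean red meat". The Discussion calls the regimen "at an intake equivalent to the current Australian dietary guidelines of 3–4 serves per week" and anticipates direct evidence that "the current guidelines to consume no more than 455 g of lean red meat is a safe, acceptable and effective dose".

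**Protein.** The Lean red meat section says the supply is meant to raise mean protein intake to at least 1.3 g/kg/day. It then expects "approximately 1.3 g/kg/day for 3 days/week when exercising and around 1.1 g/kg/day for the remaining 4 days". Study design gives at least 1.2 g/kg/day as the advice for follow-up.

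**Effect sizes.** Sample size calculations takes a 0.5 kg difference in lean mass (SD 0.9 kg) and an 18% difference in leg strength (SD 30%) from the earlier study in older women. For cognition it hypothesises that "exercise combined with a modest increase in dietary protein (1.3 g/kg/day) will lead to a medium effect". The Background describes the earlier study as giving the same two servings on most days of the week, and asks whether less frequent consumption works equally well.

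**The concern.** Three things that should match do not clearly match: the meat assigned, the intake targeted, and the intake behind the assumed effect.

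If total red meat in the meat arm is above the ceiling, the trial says something about its own regimen but cannot support a statement about an intake held at or below 455 g a week. If 1.3 g/kg/day is a weekly mean, the regimen is forecast to miss it. If it is a training-day figure, the target and the basis for the cognitive effect need to say so. If the lean-mass effect depends on how often meat is eaten, the stated power belongs to a larger effect than this regimen may produce.

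**Working it through.** **Weekly meat.**
- Inputs: two servings, 80 g cooked, three days (Abstract, Study design); ceiling 455 g cooked a week (Background).
- 2 × 80 = 160 g a day, which reproduces the daily figure. 3 × 160 = 480 g a week.
- 480 − 455 = 25 g; 25/455 = 5.5%.
- Rounding: 455/6 = 75.8 g a serving would meet the ceiling exactly. If about 80 g means anything from 75 to 85 g (assumption), the supplied total runs from 6 × 75 = 450 g to 6 × 85 = 510 g. At most 5 g a week is then left under the ceiling for red meat on the four usual-diet days.

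**Weekly protein.**
- Inputs: 1.3 g/kg/day on 3 days and 1.1 on 4 (Lean red meat).
- (3 × 1.3 + 4 × 1.1)/7 = 8.3/7 = 1.19 g/kg/day.
- Rounding both inputs down: (3 × 1.25 + 4 × 1.05)/7 = 1.14. Rounding both up: (3 × 1.35 + 4 × 1.15)/7 = 1.24. Neither reaches 1.3.
- Alternative: the 1.3 reported from the earlier trial was itself a weekly mean, with meat on k days (k is not given). Three meat days at the same gain per meat day then give 1.1 + 0.6/k: 1.25, 1.22, 1.20 and 1.19 for k = 4, 5, 6 and 7. All are below 1.3.

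**Power.**
- The Abstract and Participants section give 152 in all, while Sample size calculations says 152 in each group. That is a separate discrepancy. Taking 152 in all: 76 per group, and 76 × 0.8 = 60.8, about 61 after 20% drop-out.
- Two-sample t-test, two-sided 5%, SD 0.9 kg, difference 0.5 kg: power 86%. The plan's claim of more than 80% is reproduced. For strength (18%, SD 30%) power is 91%.
- Illustration for smaller effects, assuming the effect shrinks in proportion to meat days (0.5 × 3/k):

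| Earlier trial's meat days k (assumed) | Scaled difference | Power at 61 per group |
|---|---|---|
| no scaling | 0.50 kg | 86% |
| 4 | 0.375 kg | 63% |
| 5 | 0.30 kg | 45% |
| 6 | 0.25 kg | 33% |
| 7 | 0.21 kg | 26% |

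**The case against.** The case on the other side is substantial, and much of it stands.

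- **The 25 g excess is within rounding.** Several sections mark the serving weight as approximate, so 480 against 455 g is not on its own a contradiction. What remains is that the supply uses up the whole allowance and usual-diet red meat comes on top, in an amount the protocol does not give.
- **Serves.** A reader might infer that six servings contradict the 3–4 serves in the Discussion. The protocol does not define a guideline serve. The one other beef serving it mentions, 113 g, would make 480 g about 4.2 serves. That contradiction is not established.
- **Meaning of the mean.** Elsewhere the text uses mean and average for group averages, so the 1.3 target could be a group mean on training days, and the 3-day/4-day split is disclosed in the same paragraph. That reading is possible, but the target sentence does not say it and Sample size calculations uses 1.3 without limiting it to training days. The wording is ambiguous; nothing is concealed.
- **Size of the contrast.** A reader might infer that the protein contrast is under half of the earlier one: (1.19 − 1.1)/0.2 = 43%. With the same portion the ratio is 3/k, which is 75% to 50% for 4 to 6 meat days and 43% only for meat every day. The documents say most days, so 43% is the extreme.
- **Proportional scaling.** The documents do not support it. Their rationale leans on protein per dose around exercise, and the meat falls on training days. The present trial is also longer (24 weeks against 4 months), and controls are steered below 1.1 g/kg/day, which could widen the contrast. So the table cannot be read as the trial's true power.

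**Conclusion.** The concern holds as an inconsistency in the intake figures and in the scope of the planned conclusion.

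1. Supplied red meat is about 480 g a week, at or slightly above the 455 g ceiling, and usual-diet red meat is unrestricted on four days. The design therefore cannot deliver the anticipated direct evidence on that ceiling, although it can speak to its own regimen.
2. The forecast weekly mean protein is about 1.19 g/kg/day (1.14 to 1.24), against a target worded as a mean of at least 1.3. The cognitive effect rests on an unqualified 1.3, and the follow-up advice uses a third figure, 1.2.
3. The power claim is arithmetically right at 0.5 kg. It assumes that three meat days are as effective as the earlier trial's most days, which is the question the Background poses. If the effect is smaller, power falls below 80%: for example 63% at 0.375 kg and 26% at 0.21 kg. How much smaller, if at all, the documents do not say.

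Randomisation, outcomes and the comparison between groups are unaffected. What is affected is the stated target, the headline claim and the basis of the effect size.

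**What to change.** - Reconcile the Background, Study design, Lean red meat, Sample size calculations and Discussion on the weekly amount of meat, and on whether 1.3 g/kg/day is a training-day or a weekly figure. Bring the follow-up figure of 1.2 into line with the answer. Which amount is right is for the investigators.
- Word the conclusion for the regimen assigned, and report total red meat actually eaten, supplied plus habitual. The compliance calendar covers supplied meat only, so the habitual part has to come from the food diaries.
- Derive the meat group's weekly protein and red meat intake by weighting the meat-day and non-meat-day diaries 3/7 and 4/7. For protein the gain is small on the forecast figures (1.19 against an unweighted 1.20). For meat it matters: the supplied portions alone would appear as (160 + 0)/2 × 7 = 560 g a week unweighted, against 480 g weighted.
- State that 0.5 kg is carried over from a more frequent regimen, and show power for a range of smaller effects, labelled as an assumption: 0.375 kg 63%, 0.30 kg 45%, 0.21 kg 26%.

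The cost is protocol wording, derived variables from diaries already planned, and a more modest claim. No new data collection is needed.
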